| 
Primary objectives:
 
To compare the efficacy of a personalized treatment of nephrotic iMN driven by anti-PLA2R1 antibody epitope profile at month 0 and month 6 with the GEMRITUX therapeutic protocol to induce clinical remission of the nephrotic syndrome at month-12.
 
Secondary objectives:
 
To compare between a personalized treatment of iMN driven by anti-PLA2R1 antibody epitope profiles and the GEMRITUX therapeutic protocol:
 
 
- Complete clinical and immunological remissions at M6, M9, M12, M18, M24
 
- Partial clinical remission at M6, M9, M12, M18, M24
 
- Proteinuria and albuminuria at M6, M9, M12, M18, M24
 
- Changes in proteinuria and albuminuria from baseline at M6, M9, M12, M18, M24
 
- Serum creatinine and estimated glomerular filtration rate (eGFR) at M6, M9, M12, M18
 
- Changes in serum creatinine and eGFR from baseline at M6, M9, M12 and M18
 
- PLA2R1-Ab titers at M6, M9, M12, M18 and M24
 
- Serious adverse
 
 
The following objectives aim to study risk factors for remission or relapse:
 
 
- To determine risk factors for remission (immunological and clinical, partial or complete) at M12 in patients pooled from the two arms
 
 |

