## 2.2 Secondary Objectives

The following objectives are to compare between a personalized treatment of iMN driven by anti-PLA2R1 antibody epitope profiles and the GEMRITUX therapeutic protocol:

1. Complete clinical remissions at M6, M9, M12, M18, M24
2. Partial clinical remission at M6, M9, M12, M18, M24
3. Immunological remissions at M6, M9, M12, M18, M24
4. Proteinuria and albuminuria at M6, M9, M12, M18, M24
5. Changes in proteinuria and albuminuria from baseline at M6, M9, M12, M18, M24
6. Serum creatinine and estimated glomerular filtration rate (eGFR) at M6, M9, M12, M18
7. Changes in serum creatinine and eGFR from baseline at M6, M9, M12 and M18
8. PLA2R1-Ab titers at M6, M9, M12, M18 and M24
9. Recording all AEs/SAEs during study follow-up, 24 months

The following objectives aim to study risk factors for remission or relapse:

10. To determine risk factors for remission (immunological and clinical, partial or complete) at M12 in patients pooled from the two arms
11. To determine risk factors for relapse (between M12 and M24) in patient responders at M12, pooled from the two arms

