## 3. Evaluation criteria

### Principal evaluation criteria:

Clinical remission will be defined as a composite criterion combining (KDIGO definitions):

- Complete clinical remission: urinary protein/creatinine ratio (UPCR)<0.3 g/g in spot morning urine samples and Normal serum albumin and eGFR > 60 ml/min/1.73 m^2

- Partial clinical remission: UPCR < 3.5 g/g with a decrease greater than 50% from baseline and improvement or normalization of the serum albumin concentration and increase of serum creatinine lower than 20%

Secondary evaluation criteria:

1. Complete clinical remission as defined above
2. Partial clinical remission as defined above
3. Immunological remission: full PLA2R1 depletion measured by ELISA (titer<14RU/ml)
4. Proteinuria and albuminuria are measured on urine sample (proteinuria-to-creatinine ratio or albuminuria-to-creatinine ratio g/g) or collected during one day (g per day)
5. Change in proteinuria are measured in percentage change in proteinuria from baseline to M6, M9, M12, M18, M24
6. Serum creatinine is measured in blood sample in  $\mu\text{mol/l}$  and eGFR using the CKD-EPI formula.
7. Change in serum creatinine and eGFR are measured in percentage change from baseline to M6, M9, M12, M18, M24
8. PLA2R1-Ab titer are measured by ELISA in RU/ml
9. Severe infections are defined as infections that led to hospitalization during study follow-up
10. Remission will be defined as already stated. Patients from both groups will be analysed jointly. The following risk factors will be studied in this analysis:
  - Lymphocyte counts: B cells (CD19, transitional, mature and memory) and T cells (CD3, CD4, CD8 and TReg) measured in blood sample at J0, M3, M6, post-rituximab infusion
  - Serum level of cytokines (pg/ml) measured in blood sample at J0, and after first remission (or M24 if no remission)
  - Residual serum rituximab levels ( $\mu\text{g/ml}$ ) measured in blood sample at M3 post-rituximab infusion using ELISA
  - Neutralizing anti-rituximab antibodies (ng/ml) measured in blood sample at M3 and M6 post-rituximab infusion
11. Responders are patients entered in partial or complete remission at M12. Relapse is defined by an increased proteinuria > 3.5 g/g after remission at M12. Patients from both groups will be analysed jointly. The risk factors studied will be the same as above measured at J0, M3, M6, M9 and M12 post-rituximab infusion.

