#### 5. Benefit/ Risk

##### Benefit

- At the individual level:

Our recent works on the identification of nephrotoxic autoantibody activity should contribute to improve the individual management of patients with MN, and help to better select patients who should benefit from early and aggressive immunosuppressive strategies. Patients in the personalized arm should expect a remission rate around 85% at 12 months.

- At the collective level:

If the personalized strategy is validated, we should improve the remission rate and decrease the risk of serious adverse events in iMN treatment. Moreover, ancillary studies will help us to understand resistant forms of iMN and proposed new immune therapy like inducing TReg therapy, or Memory B-cell targeting in recurrent forms.

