### 10.3 Adverse Event Reporting

An adverse event is any condition that occurs after enrollment, whether or not considered related to study treatment. Signs and symptoms existing prior to study and documented on the baseline Medical History form or Physical Examination Form are not considered AEs. Only baseline signs and symptoms that worsen while the subject is on the study drug are considered adverse events.

At every visit, participant will be questioned regarding the occurrence and nature of any adverse experiences. If any signs, symptoms or the results of the laboratory tests indicate an adverse effect, the study physician should determine the severity (grade) of the AE and judge the relationship to the study treatment. In addition, if an adverse event necessitates medical care, appropriate care will be provided. Adverse events should be documented on the Adverse Event Report form, regardless of relationship to the study drugs. Notably, AEs thought to be due to treatment with the study drug are still reported as AEs in this study. The following information will be collected for all Adverse Events:

- Start and stop dates
- Severity (See the Severity Grading section below)
- Relationship to study drugs (See the Association with the Study Drug below )
- Action taken with study drugs
- Treatment for the AE and outcomes

The only circumstance in which an Adverse Event Report Form will not be filled out will be isolated lab value abnormalities of grade 1 severity.

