### **12.3.2 Analysis of the main secondary objective:**

The secondary objectives consist in comparing several parameters between both treatment groups (GEMRITUX versus Personalized treatment) at different study timepoints according to each specific objective. The secondary assessment criteria can be grouped into two categories:

- Objectives 1, 2 and 3: binary criteria (remission clinical or immunological), compared at different timepoints between the two groups. Comparisons will be performed using a Chi-square test or Fisher's exact test in case of small sample.
- Objectives 4, 6 and 8: quantitative criteria compared at different timepoints between the two groups. Comparisons will be performed using a student t-test (or mann-whitney rank sum test in case of non-parametric variables).
- Objectives 5, 7: Quantitative criteria evolution (changes from baseline), defined as the difference between the  $M_x$  and  $D_0$  values,  $\Delta\text{variable} = \text{Variable } M_x - \text{Variable } D_0$ . Analyses will use an analysis of covariance which takes into account the initial values as a covariate. The dependent variable will be the  $\Delta\text{variable}$  and the variable of interest the treatment group.
- Objective 9: Severe infections will be described by type and their frequencies, absolute and relative, presented. The rate of patients presenting with at least one severe infection during follow-up will be compared between the two groups using a Chi-square test or Fisher's exact test in case of small sample.

Further multivariate analyses will be eventually discussed in case of imbalanced potential confounding factors between the groups.

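### Secondary objective 9 covers all AEs/SAEs over 24 months, but its criterion and its analysis cover only infections leading to hospitalization, so overall and non-infectious SAEs have no planned between-arm analysis

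*Protocol*

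**What the plan says.** Section 2.2 opens its first list of secondary objectives with a comparative stem: "The following objectives are to compare between a personalized treatment of iMN driven by anti-PLA2R1 antibody epitope profiles and the GEMRITUX therapeutic protocol". Item 9 of that list is "Recording all AEs/SAEs during study follow-up, 24 months". The Summary's own list of between-arm objectives ends with a fragment, "Serious adverse".

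Section 3 gives secondary criterion 9 as: "Severe infections are defined as infections that led to hospitalization during study follow-up".

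Section 12.3.2 assigns analyses by objective number and states: "Objective 9: Severe infections will be described by type and their frequencies, absolute and relative, presented". It then specifies the test: "The rate of patients presenting with at least one severe infection during follow-up will be compared between the two groups using a Chi-square test", with Fisher's exact test for small samples. Nothing else in Section 12 mentions AEs or SAEs.

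In Section 5 the collective benefit, should the strategy be validated, is that "we should improve the remission rate and decrease the risk of serious adverse events in iMN treatment".

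The data needed for a wider endpoint are already required. Section 10.3 introduces its list of items with "The following information will be collected for all Adverse Events", and Section 10.5 has investigators report SAEs to the sponsor within 24 hours, subject to the limited exceptions in Section 10.7.

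**The concern.** One numbered objective has two scopes. An analyst who follows Section 2.2 would compare all AEs and SAEs between arms. An analyst who follows Sections 3 and 12.3.2 would compare one kind of SAE and stop. A separate statistical analysis plan can add detail, but it should not have to decide which protocol section governs.

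The gap matters because the two strategies differ in when and how much rituximab is given. Section 7.1 puts patients with CTLD1/7 activity at about 70%, which is roughly 22 of 32 in the personalized arm (0.70 × 32 = 22.4). They are assigned rituximab at month 0, while controls have six months of symptomatic treatment first. Harms could therefore move in either direction. Section 5 names infusion reactions, infections and cardiovascular events as the most frequent serious reactions to the drug. Section 10.8 lists death, dialysis, thrombosis, severe denutrition and severe infection as expected from the disease. Section 14 singles out dialysis, cardiovascular events and deaths for the monitoring committee. Of all these, only infection has a planned comparison by arm.

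The trial is also open label. Settling the safety endpoint before results are seen protects it from the charge that the reported events were chosen afterwards.

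**Working it through.** **1. Do the numbered items correspond?** Sections 2.2 and 3 both run from 1 to 11, and the subjects match item by item: complete remission, partial remission, immunological remission, proteinuria and albuminuria, their change, creatinine and eGFR, their change, antibody titre, then at 10 and 11 the risk factors for remission and relapse. Section 12.3.2 uses the same numbers. Item 9 is the one place where the subject changes:

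| Place | Scope of item 9 |
|---|---|
| Section 2.2, objective 9 | all AEs and SAEs, 24 months, under a comparative stem |
| Section 3, criterion 9 | infections leading to hospitalization |
| Section 12.3.2, Objective 9 | patients with at least one such infection, compared by arm |

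**2. What does the narrower scope leave out?** Section 10.1 defines an SAE as an event that is fatal, life-threatening, disabling, a congenital anomaly, leads to or prolongs hospitalization, or is an important medical event. An infection leading to hospitalization meets that definition, so criterion 9 is a subset of SAEs. Every SAE that is not an infection lies outside it.

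**3. What could a comparison of patients with any SAE deliver?** There is no planned figure to reproduce, because the protocol states no SAE rate. The rates below are assumptions, chosen to span a range.

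Inputs: 64 patients randomized 1:1 (Sections 7.2 and 8.3), hence n = 32 per arm; two-sided 5% level (Section 12.1).

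Exact power is the sum, over all pairs of event counts (i, j), of Bin(i; 32, p1) × Bin(j; 32, p2) wherever the two-sided Fisher p-value is at most 0.05. The approximate 95% half-width of the risk difference is 1.96 × √[p1(1 − p1)/32 + p2(1 − p2)/32]. For 10% vs 20% this is 1.96 × √(0.09/32 + 0.16/32) = 1.96 × 0.0884 = 0.173.

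| Assumed rates of any SAE | Exact Fisher power | Approximate 95% half-width |
|---|---|---|
| 10% vs 20% | 0.109 | ±17 points |
| 15% vs 30% | 0.215 | ±20 points |
| 20% vs 40% | 0.329 | ±22 points |
| 10% vs 30% | 0.411 | ±19 points |

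So the added comparison would be mainly descriptive. That argues for a risk difference with its interval rather than reliance on a p-value.

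**4. Does the choice of endpoint by itself decide the power?** No. At 32 per arm, infections at 5% vs 10% give 0.023 and any SAE at 10% vs 30% gives 0.411, but these are a 5-point and a 20-point difference. With a 20-point difference for infections, 5% vs 25%, power is 0.484. With a doubling for any SAE, 10% vs 20%, it is 0.109. The contrast follows the assumed effects, not the endpoint.

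**The case against.** The strongest defence is that objective 9 is worded as recording events, so the sponsor may have meant to record everything and test one prespecified safety variable. Hospitalized infection is a defensible choice for that variable. It is an SAE, Section 5 lists infection among the most frequent serious reactions to rituximab, and Section 10.8 lists severe infection as expected from the disease, so the endpoint is not blind to disease harm. Dialysis, cardiovascular events and deaths go to the monitoring committee under Section 14. Descriptive SAE tables are ordinary content for a statistical analysis plan, which is not at hand. The Summary's fragment may have been cut in text extraction and is weak evidence.

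Much of this stands. Severe infection should stay as a compared variable; replacing it would be a preference. A single any-SAE proportion could also let more drug harm and less disease harm cancel out, which is why a breakdown by event type is needed. But the defence does not remove the mismatch. Objective 9 sits under a stem that says its items are compared between arms, and Section 12.3.2 claims by number to analyse that objective while covering only part of it. Passing events to a committee is not a comparison by arm.

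A reader might go further and infer that the trial cannot support or refute its own claim about SAEs. The protocol does not bear this out. The sentence in Section 5 is a conditional expectation, not a hypothesis; one component of SAE risk is compared; and the remaining data are collected and could be tabulated. A reader might also infer that hospitalized infection is a far less powerful endpoint than any SAE. The power figures show this only when unequal effects are assumed.

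**Conclusion.** The inconsistency is real and lies within the protocol: objective 9 is broader than the criterion and the analysis that carry its number. Following the plan as written leaves overall SAEs and all non-infectious SAEs without a planned between-arm analysis, although Section 5 anticipates fewer serious adverse events. This rests on the text alone and needs no assumed rate.

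Its consequence is limited to safety conclusions. Correcting it would give an estimate with an interval of roughly ±17 to ±22 percentage points under the assumed rates, and power of 11% to 41%. It would not give a confirmatory SAE test. It should be corrected because it is cheap and concerns the only safety variable with a planned comparison.

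**What to change.** Make Sections 2.2, 3 and 12.3.2 agree, and complete the Summary item if it is incomplete in the source document:

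- In criterion 9 and the Objective 9 analysis, add the proportion of patients with at least one SAE of any cause, as defined in Section 10.1, from randomization to M24.
- Present it by arm with the risk difference and 95% CI, and state that it is an estimate and not a confirmatory test.
- Break it down by event type, including thrombosis, dialysis, cardiovascular events, serious infusion reactions and death.
- Keep infections leading to hospitalization as a named component with its existing comparison.
- Reconcile the SAE row in the schedule of assessments, which is limited to treatment-related events, with Sections 2.2 and 10.3, which are not, so that any-cause SAEs are captured consistently.

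The cost is protocol wording and one more table. Treatment, visits and sample size are unchanged, and reporting of AEs and SAEs is already required by Sections 10.3 and 10.5. The drawback is an imprecise estimate that will need careful wording in the report.

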#### **M6 visit = 6 months after randomization +/-15 days**

- Consultation date
- Clinical examination: weight, blood pressure, edema
- Serious adverse events
- Changes in concomitant treatments
- Blood and urine lab results
- Estimated GFR CKD EPI
- Centralized assays for both arms:
  - 2 dry tubes of 5 ml of blood and 2 EDTA tubes of 3 ml of blood will be shipped to Nice at room temperature for PLA2R1-Ab, epitope profile determination, serum rituximab levels, anti-rituximab antibodies, and, B and T cells counts (see manual lab)
- **In the GEMRITUX arm**
  - If disease still active (UPCR remains > 3.5 g/g and albuminemia < 30 g/l): plan two 375 mg/m^2 Rituximab infusions at 1-week interval (+/- 2 days) between 5 and 14 days after M6 visit.
  - If remission (partial or complete, see p.12): symptomatic treatment to be continued.
- **In the personalized arm/ Patients who received RTX at M0**
  - If remission (partial or complete, see p.12): symptomatic treatment to be continued alone and contraception will be required during 12 months after the end of the treatment.
  - If disease still active / Restricted anti-CysR activity: plan two 375 mg/m^2 rituximab infusions at 1-week interval (+/- 2 days) between 5 and 14 days after M6 visit.

- if disease still active / Anti-CTLD1/7 activity: plan two 1g rituximab infusions at 2-week interval (+/- 2 days) between 5 and 14 days after M6 visit. For patient who will develop anti-rituximab antibodies, treatment with human anti-CD20 is widely recommended.

*NB: If the patient still active disease / anti-PLA2R1 Ab-; the symptomatic treatment should be optimized*

- **In the personalized arm/ Patients who received 6-month symptomatic treatment**

- If remission (partial or complete, see p.12): symptomatic treatment to be continued
- If disease still active / Restricted anti-CysR activity: plan two 375 mg/m^2 rituximab infusions at 1-week interval between 5 and 14 days after M6 visit.
- if disease still active / Anti-CTLD1/7 activity: plan two 1g rituximab infusions at 2-week interval between 5 and 14 days after M6 visit.

**For all:** plan M9 +/-15 days and hand out a prescription to the patient for blood and urine analyses\*

\* Blood sample: urea, creatinine, electrolytes (sodium, potassium, chloride, bicarbonate), protein, albumin, full blood count.

Spot morning urine sample: protein, albumin, urea, creatinine.

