### **At the first remission**

One tube of lithium heparin of 4 ml of blood (for cytokine profile analysis) will be performed at the first remission and shipped to Nice at 4°C. If the sample cannot be collected during the visit when the remission is first confirmed, it must be collected at the following visit or at M24 for all patients that have not entered remission until the end of study.

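### The analysis of risk factors for remission at M12 includes a cytokine sample that remission itself triggers, and Section 3 does not settle the date from which the other markers are timed

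*Protocol*

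**What the plan says.** Section 2.2 sets two pooled risk-factor objectives. Objective 10 is "To determine risk factors for remission (immunological and clinical, partial or complete) at M12 in patients pooled from the two arms". Objective 11 is "To determine risk factors for relapse (between M12 and M24) in patient responders at M12, pooled from the two arms".

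Section 3 fixes the candidate predictors and their timing. For remission, criterion 10 lists:
- lymphocyte subsets, "measured in blood sample at J0, M3, M6, post-rituximab infusion";
- cytokines: "Serum level of cytokines (pg/ml) measured in blood sample at J0, and after first remission (or M24 if no remission");
- residual rituximab level at M3 after the infusion;
- antibodies to rituximab: "Neutralizing anti-rituximab antibodies (ng/ml) measured in blood sample at M3 and M6 post-rituximab infusion".

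For relapse, criterion 11 says: "The risk factors studied will be the same as above measured at J0, M3, M6, M9 and M12 post-rituximab infusion".

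The visit plan confirms how the second cytokine tube arises: "One tube of lithium heparin of 4 ml of blood (for cytokine profile analysis) will be performed at the first remission". Under that subsection, a missed tube moves to the next visit, and patients who never remit are sampled at M24. The schedule of assessments shows cytokines at M0 and at first remission only.

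The M6 to M24 visits in Section 8.5 are counted from randomization. Control patients with active disease at M6, and personalized-arm patients who had symptomatic treatment and still have active disease, receive their first infusion "between 5 and 14 days after M6 visit".

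**The concern.** A risk factor has to be measured before the event that it is meant to predict. The second cytokine sample is not: whether and when it is drawn depends on the outcome. A cytokine that merely changes when disease goes quiet would then appear to predict remission. The protocol wants to use these markers to understand resistance to rituximab, so the direction of the association matters.

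The other markers raise a separate question. If their months are counted from infusion, as Section 3 says, some of them coincide with or follow the outcome in patients who start rituximab at M6. Some are also requested at times when the schedule collects nothing.

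**Working it through.** The protocol gives no figure for these analyses, so there is nothing to reproduce. The check compares dates and counts the patients concerned.

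**1. Cytokines against remission at M12.**
- A patient first in remission at M6, M9 or M12 is sampled at that visit, in remission, or at the next one.
- A patient never in remission is sampled at M24, 12 months after the outcome was assessed.
- A patient who first remits at M18 counts as a non-remitter at M12 but is sampled in remission.

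In none of these cases does the second sample precede the first remission. Only the J0 sample does so for everyone.

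*Illustration, with assumed inputs.* Take 58 patients (2 × 29) and a remission rate of 62.5%, the mean of the planned 45% and 80%. The marker has no prognostic value and only shifts with current disease state. Non-remitters are assumed still active when sampled; late remitters would dilute the effect. With a t-test at 5% and 4,000 simulated trials:

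| State effect | J0 sample, share significant | Remission-triggered sample, share significant |
|---|---|---|
| 0 | about 5% | about 5% |
| 0.5 SD | about 5% | about 44% |
| 1 SD | about 5% | about 94% |

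**2. The rituximab clock for patients first infused after M6.**

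Month from randomization = 6 + (5 to 14 days) / 30.44 + months since infusion. The delay is 0.16 to 0.46 months.

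| Months since infusion | Month from randomization | Position |
|---|---|---|
| 3 | 9.2 to 9.5 | before the M12 outcome; close to the M9 visit |
| 6 | 12.2 to 12.5 | at or just after the M12 outcome |
| 9 | 15.2 to 15.5 | in the relapse window; no visit |
| 12 | 18.2 to 18.5 | in the relapse window; close to the M18 visit |

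Adding the ±15 days (0.49 months) of the M6 visit widens the 6-month row to 12.16 − 0.49 = 11.7 and 12.46 + 0.49 = 13.0. The sample therefore cannot be relied on to precede the outcome. At M18, lymphocytes are still counted, but the schedule no longer draws rituximab level or anti-rituximab antibodies.

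For patients first infused just after randomization, the two clocks differ only by the same 5 to 14 days, which is within the visit window.

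**3. How many patients start at M6.** Assume 32 per arm, no losses, and infusion of everyone not in remission at M6.
- *Section 7.2 rates.* 10 to 21% remit on symptomatic treatment. This is a one-year figure used here as a proxy for M6. Controls: 32 × (0.79 to 0.90) = 25.3 to 28.8. Personalized arm, CysR-restricted and not remitting (Section 7.1): 32 × 0.30 × 0.50 = 4.8. Total 30.1 to 33.6, or 47 to 53% of 64.
- *Section 1.3 rates with the 30/70 epitope mix of Section 7.1.* Remission by M6 is 0.30 × 0.43 + 0.70 × 0.0005 = 13% to 0.30 × 0.50 + 0.70 × 0.17 = 27%. Controls: 32 × (0.73 to 0.87) = 23.4 to 27.9. Personalized arm: 9.6 × (0.50 to 0.57) = 4.8 to 5.5. Total 28 to 33.

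Both routes give roughly half of the 64.

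**The case against.** The strongest reply is that the rituximab clock may be loose wording. The Summary and Section 8.4 use post-treatment for the ordinary visits of all patients, and the Summary explains the term as symptomatic treatment or rituximab. Criterion 11's list of J0, M3, M6, M9 and M12 is exactly the visit list up to M12, and exactly the visits at which anti-rituximab antibodies are drawn. Read that way, every non-cytokine marker falls before M12 in criterion 10 and at or before M12 in criterion 11. This stands as a possible reading. Against it, Section 3 says after rituximab infusion, and Section 1.4 uses the same clock for B cells, although for an ancillary study. The text supports both readings, which is why it needs reconciling.

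A reader might infer more than the protocol supports:
- *That the cytokine fault carries over to relapse.* It generally does not. Among M12 responders, first remission comes by M12, so that sample normally precedes a relapse between M12 and M24. The exception is a tube postponed to the following visit, which is M18 for a first remission at M12.
- *That all predictors are compromised.* J0 values and the 3-month post-infusion sample precede M12 on either clock. The rituximab level in criterion 10 is a 3-month value and is unaffected.
- *That untreated patients drop out, or that pooling excludes adjustment for arm.* The protocol says neither. Untreated patients still have J0 cytokines and lymphocyte counts at every visit. Covariates and the handling of untreated patients may properly be left to the SAP.
- *That the count of M6 starters is firm.* Infusion requires both UPCR above 3.5 g/g and albumin below 30 g/L, so some non-remitters would not be infused. The count leans high.

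**Conclusion.** The cytokine point holds under any reading of the clock. As written, criterion 10 treats a consequence of the outcome as a risk factor for it, and a marker with no prognostic value could be reported as predictive. The error rates in the illustration depend on the assumed state effect; the direction of the fault does not.

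The timing point is conditional. If Section 3 means months since infusion, the 6-month lymphocyte and antibody samples reach the M12 outcome, and the 9- and 12-month samples fall inside the relapse window, for roughly half of the 64 patients. If it means visit months, this part disappears. The documents do not decide between the two.

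Both points concern objectives 10 and 11, which are exploratory. The randomized comparison of remission at M12 is untouched. The change should be made, but the trial does not depend on it.

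**What to change.** Amend the wording of Section 3:
- **Cytokines.** Use only the J0 sample as a predictor of remission. Report the second sample descriptively, as change from J0.
- **Time origin.** State one clock for criteria 10 and 11, and reconcile it with Section 1.4, the Summary, Section 8.4 and the schedule of assessments.
- **Order in time.** Admit only samples drawn before the outcome. For remission, that means before the M12 assessment. For relapse, it means up to M12, with a landmark at M12. The remission analysis should keep the M9 visit sample. A cut-off at M6 would discard the only post-infusion sample before M12 in patients who start at M6, and 3 months after infusion is the timepoint that Section 1.3 links to remission.
- **Drug markers.** Analyse rituximab level and anti-rituximab antibodies in treated patients, by time since infusion.

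The cost is wording and fewer timepoints usable as predictors. No new samples or visits are required.
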